## Outcome measures

The primary outcome is the HbA_1c_ at the end of the 13-week RCT phase, comparing AHCL to usual care with adjustment for baseline HbA_1c_. Secondary outcomes will be assessed prior to randomization and during the final 2 weeks of the RCT. Recording of safety measures (DKA, severe hypoglycemia, hospitalizations, issues related to use of study devices) will be ongoing throughout the study. The schedule of primary and secondary outcome assessments is presented in Table 1.

**Table 1 Tab1:** Study assessments

	Baseline	13 weeks	26 weeks	39 weeks	52 weeks
HbA_1c_	X	X	X	X	X
Glycemic metrics^a^	X	X	X	X	X
Psychosocial metrics^b^	X	X			
Sleep^c^	X	X			
Platform performance^d^	X	X	X	X	X
Safety^e^	X	X	X	X	X
Qualitative study^f^		X			

^a^Time in range 70–180 mg/dL (3.9–10 mmol/L); time in tight range 70–140 mg/dL (3.9–7.8 mmol/L); time < 70 mg/dL (3.9 mmol/L); time > 180 mg/dL (10 mmol/L); hypoglycemic events; day-time (0600–2359 h) and night-time (0000–0559 h) TIR. ^b^Hypoglycemia Fear Survey; Diabetes Treatment Satisfaction Questionnaires; Insulin Dosing Systems: Perceptions, Ideas, Reflections and Expectations. ^c^Pittsburgh Sleep Quality Index; Patient-Reported Outcomes Measurement Information System Sleep Disturbance and Sleep Impairment questionnaires; habitual sleep patterns via accelerometery. ^d^Alarm frequency; percentage time of SmartGuard™ use/sensor wear; SmartGuard™ exits. ^e^Diabetic ketoacidosis; severe hypoglycaemia; hospitalizations; any issues related to device use. ^f^Interviews will commence following completion of the 13-week RCT phase.

### HbA_1c_

HbA_1c_ will be measured by a calibrated point-of-care device (either DCA Vantage Analyzer, Siemens Healthcare Diagnostics, Swords, Ireland, or Cobas B 101, Roche Diagnostics, Rotkreuz, Switzerland). The same analyzer system will be used throughout the study at respective study centers. If HbA_1c_ at screening is above the detection range of the point-of-care device (> 14% [130 mmol/mol]), all subsequent HbA_1c_ tests for this participant will be performed by a formal diagnostic laboratory.

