
### Study procedures

At screening/enrolment (Visit 1), prior to the start of any study-related procedures, written informed consent/assent will be obtained from participants and, if applicable, their legal guardians (for participants aged 7 to 15 years, and inclusive). Subsequently, demographic and anthropometric data, date of T1D diagnosis, current insulin therapy, prior CGM use, and co-morbidities will be recorded. Episodes of diabetic ketoacidosis (DKA) and severe hypoglycemia (defined as coma or convulsion requiring assistance from others) within the previous 12 months will be collected. Female participants of child-bearing potential will perform a urine pregnancy test. To confirm eligibility, HbA_1c_ will be measured by a calibrated point-of-care device. All participants will commence 2-week blinded CGM (Guardian™ Sensor 3 and Link 3 transmitter, Medtronic, San Francisco, CA) for continuous collection of baseline glycemic data. Participants will be instructed to perform self-monitoring blood glucose (SMBG) calibration at least 3 times daily during this phase (Contour Next Link 2.4 m, Medtronic). Questionnaires for participant-reported psychosocial and sleep outcomes will be administered, and habitual sleep patterns will be recorded using actigraphy prior to randomization.

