### Randomization

Prior to study commencement, a randomization sequence for a 1:1 allocation with permuted blocks of random size, stratified by pre-randomization HbA_1c_ (8.5–11.2%, or ≥ 11.3% [69–99 mmol/mol, or ≥ 100 mmol/mol]) and age (aged 7–15 years, or aged 16–25 years) will be generated by a biostatistician using Stata 17.0 (StataCorp, College Station, TX) and imported into the Research Electronic Data Capture (REDCap) randomization module [36]. The REDCap project will subsequently be moved into production, rendering the randomization sequence inaccessible and preserving allocation concealment. Participants will be randomly allocated to the intervention arm (commence AHCL) or control arm (continue standard care) following baseline data collection using the randomization module. Participants and study staff will not be blinded to this intervention assignment.

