### Statistical analysis

Statistical analyses will be performed using the up-to-date version of specialist statistical software (R, SAS, or Stata), and results will be reported in line with the CONSORT statement. The biostatistician will be blinded to intervention assignment and will use non-informative group codes until all analyses are completed. Appropriate descriptive statistics will be presented for all variables, including means and standard deviations for continuous normally distributed variables and counts and percentages for categorical variables. The primary analysis will follow the intention-to-treat principle, with participants analyzed as per randomization allocation. A secondary per-protocol analysis will also be conducted where only those participants in the intervention group using SmartGuard™ for at least 70% of the time will be included. An alpha of 0.05 will be considered statistically significant. Mixed effects regression models will be used to estimate mean differences in outcomes, with 95% confidence intervals and p-values between groups. Models will be adjusted for baseline and stratification variables. A random effect for site will be included. There will be no adjustment for multiple comparisons. Residuals of all models will be plotted to assess whether homoscedasticity assumptions are met. If necessary, outcome variables may be log-transformed or quantile regressions undertaken.

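### The laboratory route for HbA1c above the point-of-care range opens only after an off-scale screening result, so a first off-scale value at week 13 leaves the primary outcome censored, and the baseline may lack a number too

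*Protocol article*

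**What the plan says.** Under Outcome measures, HbA1c, the default is a point-of-care analyser: "The same analyzer system will be used throughout the study at respective study centers". There is one exception. If the screening value is "above the detection range of the point-of-care device" (given as 14%, 130 mmol/mol), "all subsequent HbA_1c_ tests for this participant will be performed by a formal diagnostic laboratory". The trigger is the screening result, and the scope is the tests that follow it.

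Under Study procedures, the only HbA1c test described before randomisation is at Visit 1: "To confirm eligibility, HbA_1c_ will be measured by a calibrated point-of-care device". Table 1 lists HbA1c at a column headed Baseline and at 13 weeks, without saying whether Baseline is the Visit 1 reading or a separate test.

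The analysis needs numbers at both times. Outcome measures states: "The primary outcome is the HbA_1c_ at the end of the 13-week RCT phase, comparing AHCL to usual care with adjustment for baseline HbA_1c". Statistical analysis adds: "Models will be adjusted for baseline and stratification variables". The Abstract describes the outcome as change from baseline to 13 weeks, which needs both values as well. The inclusion criteria set no upper limit on HbA1c.

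**The concern.** The rule leaves one gap for certain and a second one conditionally.

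- **Week 13 (certain).** A participant in range at screening stays on the point-of-care device. If the week-13 value exceeds the device's limit, the primary outcome is recorded only as above 14%. AHCL is expected to lower HbA1c, so this falls mainly on controls. Losing or flattening the highest control values makes the control mean look better and shrinks the estimated benefit.
- **Baseline (conditional).** If the Visit 1 reading serves as the baseline, a participant off-scale at screening has no numeric covariate. The week-13 value would then come from a laboratory and the baseline from a point-of-care device.

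A value that was not measured at the visit cannot be recovered later by analysis wording, which is why the measurement rule matters separately from the analysis plan.

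**Working it through.** **Inputs.** From Sample size: SD 23 mmol/mol, within-person correlation 0.6, difference 15 mmol/mol, power 90%, alpha 0.05 (two-sided assumed), 32 per group evaluable, 40 per group recruited. From Study population: entry at 69 mmol/mol or above. From HbA1c: limit 130 mmol/mol. Assumed: a normal distribution, with underlying means of 80 to 91.2 mmol/mol. The upper figure is the baseline mean of the single-arm study cited in the Introduction.

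**Step 1: reproduce the sample size.** Residual SD after baseline adjustment = 23 × √(1 − 0.6²) = 18.4. Per group, n = 2 × (1.960 + 1.282)² × 18.4² / 15² = 31.6, so 32, or 64 in total. Then 64 / 0.8 = 80. Both figures match the plan. A change-score analysis (SD 23 × √(2 × 0.4) = 20.6) would need 40 evaluable per group. The planned size therefore relies on the baseline covariate.

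**Step 2: off-scale at screening.** The proportion is P(X > 130) / P(X ≥ 69).
- Mean 80: 0.0149 / 0.684 = 2.2%, or 1.7 of 80.
- Mean 91.2: 0.0458 / 0.833 = 5.5%, or 4.4 of 80.

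**Step 3: newly off-scale at week 13.** Simulated bivariate normal values, baseline truncated at 69, underlying mean unchanged in controls, AHCL 15 mmol/mol lower.
- Controls: 1.7% (mean 80) to 3.8% (mean 91.2), or 40 × 0.017 = 0.7 to 40 × 0.038 = 1.5 participants.
- AHCL: 0.2% to 0.6%.

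Truncation makes enrolled controls drift down by regression to the mean under this model. If the mean of enrolled controls is instead held constant, the control figures become 2.9% and 5.1% (1.2 and 2.0 of 40). If it falls by 5 mmol/mol, they become 1.6% and 3.0%. The answer stays at about 1 to 2 controls.

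**Step 4: effect on the control mean (Step 3 main case).** Capping at 130 lowers it by 0.13 (mean 80) to 0.32 (mean 91.2) mmol/mol. This implies that off-scale values average about 0.13 / 0.017 = 7.6 to 0.32 / 0.038 = 8.4 above the limit.

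Dropping lowers it by p/(1 − p) × (mean of off-scale values − mean of all controls). At mean 91.2, enrolled controls average 98.1 at baseline and 91.2 + 0.6 × (98.1 − 91.2) = 95.3 at week 13. Hence 0.038 / 0.962 × (138.4 − 95.3) = 1.7. At mean 80 the result is 0.9.

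Against the target of 15, capping is 0.1/15 to 0.3/15, about 1% to 2%. Dropping is 0.9/15 to 1.7/15, 6% to 11%. The AHCL mean also moves, by less, so the difference shrinks by slightly less than these figures.

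**Step 5: effect on the baseline-adjusted estimate.** Simulation with 32 per arm, 3,000 replicates and true effect 15. Here off-scale baselines are capped or excluded as well as new off-scale week-13 values.

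| Underlying mean | Mean change in enrolled controls | All numeric: estimate, power | Capped at 130 | Excluded |
|---|---|---|---|---|
| 80 | 0 | 14.83, 0.885 | 14.63, 0.884 | 13.94, 0.848 |
| 80 | −5 | 14.88, 0.888 | 14.78, 0.888 | 14.33, 0.863 |
| 91.2 | 0 | 14.94, 0.889 | 14.56, 0.889 | 13.43, 0.819 |
| 91.2 | −5 | 15.04, 0.891 | 14.83, 0.888 | 14.03, 0.845 |

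Capping shrinks the estimate by 0.10 to 0.38 mmol/mol with almost no loss of power. Excluding shrinks it by 0.55 to 1.51 and costs 2.5 to 7 points of power.

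**The case against.** **The baseline gap may not exist.** Study procedures gives the Visit 1 test the purpose of confirming eligibility, and a two-week baseline phase follows. If the Baseline column in Table 1 is a separate later test, the existing rule already sends it to the laboratory, so baseline and week 13 would both be numeric and by one method. This stands: the article describes no such test, but a condensed article need not. The week-13 gap is unaffected.

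**Handling of censored values belongs to the analysis plan, which is not shown.** This stands for the analysis. It does not answer the measurement rule, which is fixed here and determines whether a number exists at all. The article does not say that off-scale values would be excluded or set to 130; both are possibilities used to show the size. Exclusion would also fit poorly with the stated intention-to-treat analysis.

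**The effect is small and runs toward the null.** This stands. It cannot create a false benefit, and the plan allows for 20% loss of data. Step 5 starts from 32 evaluable per arm and removes participants from that number, so its power losses are on the pessimistic side.

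**Stronger readings.** A reader might infer that the trial loses the group it was designed for. The documents do not support that: the target population is HbA1c of 8.5% or above, with particular interest above 10%, and those above 14% are a few of 80. A reader might also infer that randomisation is compromised. It is not: allocation is "stratified by pre-randomization HbA_1c" with an open upper stratum from 100 mmol/mol, so an off-scale reading still has a stratum.

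**Conclusion.** The point holds for week 13 and conditionally for baseline. As written, a participant first off-scale at week 13 has a right-censored primary outcome. This is more likely in controls (1.7% to 3.8%, against 0.2% to 0.6% on AHCL), and the bias from capping or dropping is toward no difference. Whether participants off-scale at screening also lack a numeric baseline depends on what Table 1 means by Baseline.

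The sizes rest on an assumed normal distribution and assumed underlying means, not on trial data. A heavier upper tail would raise them, and a larger fall in controls would lower them. Severity is minor to moderate: too small to threaten the trial's conclusion at the planned effect, but avoidable, unequal between arms and impossible to repair once the visit has passed.

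**What to change.** Extend the trigger from the screening result to any study HbA1c above the analyser's limit, and require a laboratory HbA1c at that same visit. For screening or baseline, the sample should be taken before randomisation; the two-week baseline phase leaves time. State whether the Visit 1 reading is the baseline value in the primary model. In the analysis plan, if it does not already say so, treat any value still off-scale as right-censored at 130 mmol/mol (censored regression, or imputation above 130), not as missing and not as equal to 130.

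The cost is a sentence or two in the protocol and a handful of laboratory tests through a route the plan already uses.

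One downside remains. For participants off-scale at screening, baseline and week 13 would both be laboratory values. For those newly off-scale at week 13, a point-of-care baseline would be paired with a laboratory outcome, mainly in controls. The fix therefore does not give one method throughout for everyone. These cases should be reported and examined in a sensitivity analysis.

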### Demographics

Demographic information including age, gender, ethnicity and address will be collected during screening. Participants can choose multiple ethnicities, however, each participant will be assigned to a single ethnicity following a prioritized system widely used in New Zealand with the hierarchical classification of Māori, Pacific, Other, and European [38]. Residential addresses will be used to assess socioeconomic status using the New Zealand Index of Deprivation 2018 which provides a deprivation score for small geographic areas defined by Statistics New Zealand. Deprivation data will be presented as quintiles (1–5) with 1 representing the least and 5 the most deprived areas in New Zealand [39].

### Anthropometry

Height and weight will be measured using calibrated instruments. Participants will be asked to wear light clothing and remove their shoes before measurements are taken. Height will be measured to the nearest 0.1 cm with a stadiometer and weight will be measured to the nearest 0.01 kg with a calibrated scale. Height and weight will be used to calculate body mass index (BMI) as per standardized formula. World Health Organization growth standards will be used for BMI z-scores [40].

### Glycemic metrics

CGM data will be collected from CareLink™ software and analyzed according to standardized CGM metrics for clinical care [41]. Time in range (TIR) will be recorded as the percentage of time with sensor glucose levels in the range 70–180 mg/dL (3.9–10.0 mmol/L); time in tight range (TITR) as the percentage of time with sensor glucose levels in the range 70–140 mg/dL (3.9–7.8 mmol/L); hypoglycemia as the percentage of time with sensor glucose levels below 70 mg/dL (3.9 mmol/L) and below 54 mg/dL (3.0 mmol/L); hyperglycemia as the percentage of time with sensor glucose levels above 180 mg/dL (10.0 mmol/L) and above 250 mg/dL (13.9 mmol/L). TIR will also be differentiated by day (0600–2359 h) and night (0000–0559 h).

### Psychosocial assessments

Psychosocial metrics will be collected through validated self-report questionnaires completed using paper forms and the order of administration will be standardized to increase reliability. Age-appropriate versions of questionnaires will be completed by children and adolescents, young adults, and, if applicable, guardians. All questionnaires will be administered in English. Where applicable, permissions and licenses for use of questionnaires were obtained.

The Hypoglycemia Fear Survey (HFS) is a measure of behaviors that people with T1D may engage in as a result of fear of hypoglycaemia and specific worries related to various aspects of hypoglycaemia [42]. Overall, higher scores reflect greater fear of hypoglycemia. A higher score on the Behavior Subscale reflects a greater tendency to avoid hypoglycemia and/or its negative consequences. A higher score on the Worry Subscale indicates more worry concerning episodes of hypoglycemia and its consequences. Participants aged 8 years and above will complete age-appropriate versions of the HFS. To accommodate the different number of items in the age-specific versions, the analysis will use mean item scores.

The Diabetes Treatment Satisfaction Questionnaire-status (DTSQs) and the DTQS-change (DTSQc) are self-report measures of a participant’s current treatment satisfaction [43, 44]. The DTSQc has been developed to overcome potential ceiling effects, where respondents score near-maximum satisfaction at baseline and would therefore show little or no improvement at follow-ups. The DTSQc will be administered only once, at the end of a study, in addition to the DTSQs at both baseline and end-of-study. Participants aged 13 years and above will complete age-appropriate versions of the DTSQs and DTSQc.

The Insulin Dosing Systems: Perceptions, Ideas, Reflections and Expectations (INSPIRE) questionnaire measures expectations of automated insulin delivery systems in people with T1D [45]. Different questionnaires exist for baseline and post-intervention assessment, which assess impacts on perception of glycemic control, activities, health complications, individual and family quality of life, and usability of the device. The INSPIRE questionnaire will be completed prior to randomization by all participants aged 8 years and above, however, only those randomized to the intervention arm will complete the post-intervention assessment at the end of the RCT.

### Sleep assessments

Sleep will be assessed using subjective and objective methods. Participants aged 13 years and above will complete the Pittsburgh Sleep Quality Index (PSQI) to assess sleep quality and timing during the previous one month to discriminate between good and poor sleep [46]. Originally developed for adults, two items related to sleeping with a bed partner will be excluded for adolescents, as previously described [31]. The PSQI generates 7 domains for subjective sleep quality, sleep latency, sleep duration, sleep efficiency, sleep disturbance, sleep medication, and daytime dysfunction, and a global score. In adolescents, scoring for the sleep duration domain will be adjusted according to participant age to reflect the number of hours of sleep recommended as different to adults [47].

Participants will also complete the Patient-Reported Outcomes Measurement Information System (PROMIS) Sleep Disturbance (SD) and Sleep-Related Impairment (SRI) short form questionnaires to assess qualitative aspects of wake function and sleep [48]. These are generic measures for gauging the severity of sleep-wake problems on a continuum, applicable across a range of health conditions. Participants aged 8 years and above will complete age-appropriate versions of the PROMIS questionnaires.

To objectively evaluate habitual sleep and wake patterns across repeated day-night cycles, participants of all ages will wear a 3-axis accelerometer (AX3, Axivity, Newcastle, UK) on the non-dominant wrist continuously for up to 7 days and 8 nights during baseline data collection and in the final 2 weeks prior to primary outcome collection. In participants aged 7–12 years, the device will additionally be worn by a guardian to assess their sleep. This device detects movement, vibrations and orientation changes at high precision and incorporates temperature and ambient light sensors to reinforce detection of periods of wear. Outputs will be processed using the count-scaled algorithm written in MatLab (Mathworks, Natick, MA, USA) to produce sleep variables related to sleep timing, quantity, quality and variability [49]. Processing will occur in either automatic mode using “time flags” for sleep onset (bedtime) and sleep offset (wake time), or for difficult files, processed under a “manual” mode where sleep onset and offset are visually identified from the activity outputs.

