### Sample size

Using a standard deviation of 23 mmol/mol and a within-person correlation of 0.6 [17, 31], a sample size of 64 (32 participants per group) would be required to determine a conservative difference in change in HbA_1c_ of 15 mmol/mol with 90% power to the alpha of 0.05 level (single arm data suggests > 15mmol/mol achievable in this population [17]). To account for 20% loss of data and participant attrition (inflated compared to other trials to allow for potentially greater loss of data due to the high-risk population), a sample size of 80 will be recruited (40 participants per group).

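### The blinding as stated leaves the visual scoring of difficult actigraphy files, part of the only objective sleep outcome, open to knowledge of arm

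*Protocol article*

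**What the plan says.** Under Sleep assessments the article describes subjective methods (PSQI and PROMIS questionnaires) and one objective method, a wrist accelerometer, introduced with the words "To objectively evaluate habitual sleep and wake patterns across repeated day-night cycles". It is worn "during baseline data collection and in the final 2 weeks prior to primary outcome collection". The raw output is then turned into sleep timing, quantity, quality and variability: "Processing will occur in either automatic mode using “time flags” for sleep onset (bedtime) and sleep offset (wake time), or for difficult files", in a manual "mode where sleep onset and offset are visually identified from the activity outputs".

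On blinding, the Randomization section says: "Participants and study staff will not be blinded to this intervention assignment". The Statistical analysis section names one masked role: "The biostatistician will be blinded to intervention assignment and will use non-informative group codes until all analyses are completed". Nothing else in the article describes masking of people who process or score outcomes.

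Sleep is a secondary outcome. The Outcome measures section states: "Secondary outcomes will be assessed prior to randomization and during the final 2 weeks of the RCT".

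**The concern.** Manual mode involves two human judgements: whether a file is difficult enough to leave the automatic route, and where sleep begins and ends on the trace. Both feed into the derived sleep variables. If the person making them knows the arm, an expectation that closed loop improves sleep can enter the data without anyone intending it.

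The questionnaires cannot be protected from this, because participants know their treatment. The accelerometer can be, because a reader of activity traces does not need to know the arm. For some people it is also the only sleep measure described. PSQI starts at age 13 and PROMIS at age 8, so 7-year-olds have the device alone, and guardians of participants aged 7 to 12 are described only as wearing the device.

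**Working it through.** The article gives no figure for this point: no share of manual files, no scoring error and no standard deviation for sleep. The check is mainly a reading of the sections against each other, followed by an illustration on assumed inputs.

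1. **Does judgement enter the outcome?** Yes. Sleep assessments says that onset and offset are placed by eye in manual mode, and it gives no rule for when a file qualifies.
2. **Can allocation be known at that point?** The second recording falls in the final 2 weeks of the randomized phase, so it is scored after allocation. Randomization leaves study staff unblinded and makes no exception for scorers.
3. **Does the masked biostatistician cover this step?** Not as written. Group codes protect the analysis of a dataset that already holds the sleep variables. They cannot undo differences introduced when those variables were produced.
4. **Does baseline adjustment remove the problem?** No. The models adjust for the baseline value, but a scoring shift that differs by arm in the follow-up files stays in the adjusted difference.

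**Illustration, all inputs assumed.** Let *f* be the share of files scored manually, taken as equal in both arms, and *b* the between-arm difference in scoring shift, in minutes, within those files. The bias in the mean difference is

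bias = *f* × *b*.

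- *f* = 5%, *b* = 10 min: 0.05 × 10 = 0.5 min
- *f* = 10 to 30%, *b* = 15 min: 0.10 × 15 = 1.5 min to 0.30 × 15 = 4.5 min
- *f* = 30%, *b* = 30 min: 0.30 × 30 = 9 min

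To see what this could do to a test, take 32 per arm from the Sample size section. That figure reproduces: the baseline-adjusted SD is 23 × √(1 − 0.6²) = 18.4 mmol/mol, which for a 15 mmol/mol difference, two-sided 0.05 and 90% power gives 32 per arm, and 64 / 0.8 = 80. It concerns HbA1c and is borrowed here only as a group size. With an assumed sleep SD of 30 to 60 minutes, the standard error is SD × √(2/32) = 7.5 to 15 minutes. With x = bias / standard error, the two-sided false-positive rate is 1 − Φ(1.96 − x) + Φ(−1.96 − x):

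- bias 0.10 × 10 = 1 min: x = 0.067 to 0.133, rate about 5.1 to 5.2%
- bias 0.20 × 20 = 4 min: x = 0.267 to 0.533, rate about 5.8 to 8.3%
- bias 0.30 × 30 = 9 min: x = 0.6 to 1.2, rate about 9 to 22%

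The result runs from negligible to material, depending almost entirely on two quantities that the article does not report.

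**The case against.** The strongest reply is that this argues from silence. The article does not say who scores the files or what that person can see. The sentence on unblinded staff closes the Randomization section and does not mention outcome processing. Coding of files and masking of scorers are details that a journal article often leaves to a full protocol or an actigraphy manual, and neither is at hand. Falling back on manual marking when automatic detection fails is openly disclosed. The trace itself is not said to reveal the arm, so bias also needs a label, or the scorer's memory, to do so.

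Much of this stands. A reader might infer that the scorers are unmasked, or that the accelerometer results are biased; the article supports neither. A reader might also infer that the whole accelerometer outcome loses its independence. That goes too far: automatic mode is the default, and by-eye placement of onset and offset is described only for difficult files. Nor does the article say that the accelerometer is there to corroborate the questionnaires, only that subjective and objective methods are both used.

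What does not fall is the gap itself. The article chooses to set out who is and is not blinded, describes a discretionary scoring step, and presents the result as objective. Taken together, those statements leave the step uncovered.

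**Conclusion.** The point holds in a limited form. As stated, the blinding allows arm-aware selection and scoring of manual-mode files, and it does not show that this will happen. The 0.5 to 9 minute range and the false-positive rates above rest wholly on assumed shares, shifts and SDs. They also suppose a consistent, arm-dependent shift across the manual files, and should not be read as estimates for this trial. The sample size is not affected. This is a minor point, worth raising because it is avoidable at almost no cost. If a fuller protocol already masks the scorers, one sentence saying so settles it.

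**What to change.** State in the Sleep assessments section that accelerometer files are relabelled with neutral codes hiding both arm and visit before anyone decides between automatic and manual mode, and that the codes stay in place until manual scoring is finished. Both steps need cover, because choosing which files to score by eye is itself a judgement. Give the criterion for a difficult file in the same place, and report the number of manually scored files by arm so that readers can judge the exposure.

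An extra analysis restricted to automatically processed files is not needed. It is ambiguous: dropping the difficult files could make the missing data selective, and forcing automatic output on them would add error.

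The cost is recoding the files before processing, plus a sentence or two of text. No extra staff, visits or measurements are required.
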